#### **7.1.4 Randomization Procedure**

Following the completion of data collection at Visit 2, the Randomization form will then be completed. If inclusion criteria are satisfied, participants will be randomized into the ASPREE study via the internet. Password protected access is required for study personnel. Staff will be required to enter their unique ASPREE Identification number along with the following key information: study site number, ASPREE participant identification number, age and gender of participant, and confirmation of inclusion / exclusion criteria. Sites will also be asked to do a repeat entry of the participant's acrostic to ensure the right person is being randomized.

Computer-generated medication numbers will be provided to trial sites through the web portal. The randomization list will be generated by an independent statistician. This arrangement will ensure that the randomization code remains inaccessible to all study staff and senior investigators. The randomization list will be generated using the STATA 'ralloc' procedure with randomization stratified for site and age (<80 yrs and ≥80 yrs). Following the completion of the randomization process by the research assistant / nurse, a study medication number will be provided. All staff remain blinded to treatment allocation through the randomization procedure. The subsequent distribution of drug is detailed in Section 8. Records of all participants who have undergone screening and randomization will be made by completing the appropriate tracking log.

#### **7.1.5 Annual Visits**

At Annual Visits, measurements undertaken at baseline (refer to sections 7.1.1 and 7.1.3) will be repeated using identical protocols, in accordance with the ASPREE Measurements and Study Activity Schedule (Table 4). Additionally, Serious Adverse Events (SAEs) and potential clinical endpoints will be collected by participant report and medical record audit (in Australia). Following notification, clinical information relating to the SAE or endpoint will be sourced through: a) medical record review and b) hospital records and discharge summaries. Specific procedures for endpoint ascertainment and adjudication have been outlined previously in sections 5.4 and 5.5, respectively, of this protocol. In order to detect new onset atrial fibrillation

during the study, research staff will measure the pulse rate at annual visits, as described above in section 6.5.9.

### **7.1.6 Participant Retention Plan**

Based on the experience of investigators in Australia (e.g. ANBP2) and in the U.S. (e.g. ALLHAT) high rates of participant retention will be achieved using multiple strategies including:

- Compliance and retention will be encouraged by 3, 6 and 9 month research staff direct phone contact interspersed with annual face-to-face visits.
- Contacts details (including alternate contacts) will be updated during face-to-face meetings. Additional contacts are used in the situation where a participant changes address without contacting the study center.
- Newsletters will be sent to family physician co-investigators and participants on a regular basis (~2-4 per year) detailing study progress.
- Anniversary Cards may be distributed to subjects on an annual basis as a reminder of their participation.
- In Australia, the study staff member and family physician co-investigator remain in contact.

If a participant is 'lost to follow-up' despite measures detailed above, the following steps will be undertaken:

- Tracking through third party contacts (details of these are updated annually). Details for up to 3 additional contacts, who do not reside at the same address as the participant, will be obtained at randomization.
- Crosschecking with morbidity and mortality registries.
- In the U.S., data linkage through Medicare numbers will provide updated medical information and clinical events in both countries.
- In Australia, the research staff member will be able to also audit practice and hospital records in the event a participant is unable to be contacted.

### **7.1.7 Telephone Contact**

Each participant will be contacted by telephone, initially if receipt of trial drug has not been registered (in Australia) or by 4 weeks after study medication is provided (in U.S.). Three, six and nine monthly phone calls after baseline and after each annual visit will be made to encourage compliance to treatment allocation. In addition, at the 6 month phone contact, site staff will also gather information about new onset of serious adverse events or potential study

endpoints. Data to be collected during the telephone calls include:

- Compliance – the research assistant / nurse will discuss the participant's adherence to medication since the previous clinic visit.
- (6 month call) Serious adverse event and endpoint notification will be achieved by participant report (clinical information relating to these events will be sourced as for Annual Visits).
- (6 month call) Katz ADLs and Living Situation.

### **7.1.8 Other Actions**

If the participant does not proceed to randomization, then the reason for non-randomization is to be documented and collected on the designated CRF.

Any test measurement result that is outside the normal range, at baseline or annual visits, will trigger a notification to the participant's GP in Australia and will be provided to the participant's regular treating physician in the U.S. Such measurements include: 3MS, CES-D, hemoglobin and glucose levels, blood lipids and triglyceride, urine albumin : creatinine ratio, and blood pressure levels (for details, see Appendix 1: Endpoints and Other Measures).

## **7.2 Case Report Forms (CRFs)**

CRFs are used to record clinical study data and are an integral part of the study and subsequent reports. The CRFs, therefore, must be legible and complete. All forms must be filled in using a black ballpoint pen and errors must be crossed out but not obliterated and the corrections must be written above or beside the error on a free space. All corrections must be initialed and dated.

CRFs will be printable by the sites via the ASPREE website for each participating family practice (in Australia) or study site. At the end of a participant visit, the research staff will transfer the data directly onto electronic CRFs that are accessible via the ASPREE website, and retain the original hard-copy CRFs and other source documents, stored in the participant's file.

CRFs must be kept current to reflect the participant's course throughout the study. Participants are not to be identified on the CRF by name. Appropriately coded identification (GP, Practice and Subject Identification Numbers) and an acrostic of the participant's initials must be used.

## **7.3 Data Analysis**

The trial will be analyzed by statisticians based at the ASPREE Data Management Center,

Department of Epidemiology and Preventive Medicine, Monash University, and the Berman Center for Outcomes Research, University of Minnesota.

### **7.3.1 Interim analysis**

Rather than stipulate interim analysis we leave consideration of this to the independent NIH-appointed DSMB. A proposed interim analysis is described in the Data and Safety Monitoring Plan of the DSMB.

### **7.3.2 Final analysis**

All primary and secondary outcomes will be in the form of time-to-event data and rate ratios will be calculated using univariate Cox proportional hazards regression to directly compare event rates between treatment groups. In analyses of secondary endpoints, death due to causes other than those specified by the endpoint and loss to follow-up (see below) will be considered as censoring events. Given the large sample size, we anticipate randomization will adequately balance baseline characteristics of participants in the two treatment groups. If necessary, a secondary set of analyses will be performed to adjust for baseline characteristics that are found to be imbalanced between groups to the extent of a 0.25 standard deviation difference in means (quantitative measures) or an odds ratio of 1.5 (binary measures). These analyses will be conducted using multivariate Cox proportional hazards regression models.

The primary and secondary endpoints will be analyzed according to intention-to-treat principles, i.e. according to the group to which participants were randomized and without reference to their actual compliance with assigned treatment. No statistical adjustment will be made for the multiple secondary endpoints in their analysis but the reporting of all secondary endpoint analyses will make clear whether the primary endpoint was statistically significant and will state the number of secondary endpoints proposed *a priori* in the study protocol.

In the survival analyses, loss to follow-up will be considered a censoring event. This equates to an assumption that data is missing at random given the participant's treatment group and the timing of their loss to follow-up. The adequacy of this assumption will be checked in sensitivity analyses that will include both a multiple imputation by chained equations (MICE) approach and adjustment for baseline covariates predictive of propensity for dropout.

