## 2 STUDY DESIGN

ASPREE is a randomized, double blind, placebo-controlled trial. Participants will be randomized remotely via the ASPREE Data Management Center web portal. For both systems, password protected access is required for study personnel. According to a computer-generated randomization schedule, participants will be allocated to 100 mg enteric coated aspirin or placebo in a ratio of 1:1. Randomization will be stratified for general practice in Australia, for regional site in the U.S. and for age (65-79 or  $\geq 80$  years).

During an initial 4 week run-in phase participants will take placebo for compliance checking. Bayer Pharma AG will supply active drug and matching placebo.

| Pre-screening | Lifestyle Profile & Screening (Visit 1)                                                                            | Run-in phase & GP visit* | Assessments & Eligibility (Visit 2) | Annual Visit (1) | Annual Visit (2) | Annual Visit (3) | Annual Visit (4) | Annual Visit (5) | Annual Visit (6) | Annual Visit (7) |
|---------------|--------------------------------------------------------------------------------------------------------------------|--------------------------|-------------------------------------|------------------|------------------|------------------|------------------|------------------|------------------|------------------|
|               | ↓                                                                                                                  | ↓                        | ↓                                   | ↓                | ↓                | ↓                | ↓                | ↓                | ↓                | ↓                |
| Time          | -4 weeks                                                                                                           |                          | 0                                   | Year 1           | Year 2           | Year 3           | Year 4           | Year 5           | Year 6           | Year 7           |
|               | There will be additional 3-month, 6-month and 9-month telephone contact (between randomization and annual visits). |                          |                                     |                  |                  |                  |                  |                  |                  |                  |

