## 10 SAMPLE SIZE AND POWER CALCULATIONS

Participants will be approximately two-thirds from Australia and one-third from the U.S and will include 4,500 minority participants. There will be an equal allocation of participants to aspirin and placebo groups. A detailed description of sample size and power calculations for the primary and secondary endpoints is provided in Appendix 2.

In brief, 19,000 participants having 3787 events will be required to have 90% power (two-sided alpha error rate of 0.05) to detect a 10% reduction (risk ratio of 0.90) in the primary endpoint with aspirin. The rationale for this effect size is described in Appendix 2. This sample size was calculated for a univariate Cox proportional hazards regression analysis using Stata (Stata Statistical Software, Release 10, StataCorp, College Station, TX, 2007) and based on the following assumptions:

- a. The effect of aspirin is described by a hazard ratio of 0.90 in an intention-to-treat analysis. This assumes a slightly stronger underlying effect that will be weakened by cross-over of participants for reasons which include the development of a non-fatal, non-disabling cardiovascular or cerebrovascular events necessitating aspirin therapy or cessation (non-compliance) with aspirin therapy. We expect 5% per annum of placebo-group participants to initiate aspirin use (or *vice versa*).
- b. Annual dementia incidence rates of 6 per 1000 for 70-74y age group, 11/1000 (75-79y), 20/1000 (80-84y), 37/1000 (85y+)  for Australian, U.S. Hispanic and U.S. White (non-Hispanic) participants. For U.S. African Americans the rates are doubled .
- c. Incident disability for one or more Katz ADL's; annual incidence rate for males= 19.6/1000, females = 26.5/1000 (these incidence rates are from the rates observed in the subset of

- ASPREE-like participants in the CHS ([name], personal communication, August, 2008) which showed similar rates in U.S. Whites and U.S. minorities).
- d. Age-specific mortality rates in Australian and U.S. White (non-Hispanic) participants are based on the 2004 Australian population census (<http://www.aihw.gov.au/mortality/data>). Age-specific mortality rates in U.S. African American and Hispanic participants are based on 2005 rates specific to each minority (U.S. CDC statistics, 2005; <http://www.cdc.gov/nchs>).

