## APPENDIX 2. SAMPLE SIZE & POWER CALCULATIONS

For the primary endpoint, a sample size can be calculated that gives the number of primary endpoint events required for ASPREE to have 90% power for their subsequent analysis by a univariate Cox proportional hazards regression model. To estimate the number of participants required to yield these events, assumptions are made for (i) the event rates that will be seen in ASPREE participants and (ii) the duration of participant follow-up during the study. Having obtained a sample size for the primary endpoint we examine the power or effect size that this number of participants gives us for each secondary endpoint. Hence, assumptions are also required for the event rates of secondary endpoints. In general, Australian event rates have been used as a basis for ASPREE participants. This is justified on the grounds that approximately two-thirds of participants will be recruited in Australia and using the lower Australian rates errs on the conservative side for sample size calculations. For example, Australian rates of all-cause mortality, cardiovascular events and cancer are lower than in the U.S. (see Table 2 of the Research Plan). For the primary outcome, population-specific rates are used where there is strong evidence that a minority group is at increased risk.

The study will have a 1:1 aspirin:placebo group allocation ratio.

All power and sample size calculations were performed with a two-sided alpha error rate of 0.05 for a univariate Cox proportional hazards regression analysis of time to first event using the 'stpower cox' command in Stata (Stata Statistical Software, Release 10, StataCorp, College Station, TX, 2007).

Assumptions used for the original sample size and power calculations include:

- Participants will be 50%, 30%, 15%, 5% in age groups 70-74 years, 75-79 years, 80-84 years, 85 years and over, respectively.
- Participants will be 45% male and 55% female.
- Based on experience with ANBP2, the effect of clustering due to recruitment by country and enrolling general physician or clinical research site will be minimal and no explicit adjustment to the number of participants needs to be made. In any case, since randomization is at the individual participant level, treatment effect is a within-cluster comparison and this protects against any concern over loss of power due to clustering.

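### The primary Cox model omits age, a randomisation stratum and the dominant predictor, and the imbalance rule for adjusted analyses cannot realistically fire for it

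*Protocol*

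**What the plan says.** Section 2 (Study design) describes the allocation: "Randomization will be stratified for general practice in Australia, for regional site in the U.S. and for age". Section 7.1.4 repeats the stratification by site and age and puts the age split at 80 years.

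Section 7.3.2 (Final analysis) sets the model for all primary and secondary outcomes: "rate ratios will be calculated using univariate Cox proportional hazards regression to directly compare event rates between treatment groups". No stratification factor enters it. The section expects randomisation to balance a trial of this size. It allows a secondary set of multivariate Cox models, if necessary, for characteristics that differ between the arms "to the extent of a 0.25 standard deviation difference in means (quantitative measures) or an odds ratio of 1.5 (binary measures".

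Baseline covariates appear in two other places. Section 7.3.2 plans a sensitivity analysis for loss to follow-up that adjusts for predictors of dropout. Section 7.3.4 plans subgroup interaction models, one of them for age below and above the study median.

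The sample size in section 10 and Appendix 2 was calculated for the same univariate Cox model: "19,000 participants having 3787 events will be required to have 90% power (two-sided alpha error rate of 0.05".

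**The concern.** The design treats age as important enough to stratify on, and the analysis then leaves it out. When a strong predictor is omitted from a Cox model, the hazard ratio being estimated moves towards 1 and some power is lost. Leaving out a factor that was balanced by design also makes the standard error slightly too large for the allocation actually used.

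The imbalance rule does not repair this. It selects covariates by the size of a chance difference, whereas the benefit of adjustment depends on how strongly a covariate predicts the outcome. In a trial of 19,000 its thresholds are far beyond what chance produces for age or for any common factor. For age, they are also close to the point where an imbalance would be as large as the effect the trial is looking for.

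**Working it through.** **1. The plan's own figures reproduce.** Inputs from section 10: hazard ratio 0.90, two-sided alpha 0.05, power 90%. From Appendix 2: 1:1 allocation.
- Schoenfeld events: 4 × (1.960 + 1.282)² / (ln 0.90)² = 3787, as stated.
- Appendix 2, after the change in recruitment: 311 + 3374 = 3685 events, giving power 89.2% (stated: 89%).

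**2. Age gradient.** For each age and sex group, the placebo hazard is 0.9 × (dementia + ADL loss + 0.5 × mortality), using the Appendix 2 rates for Australian and U.S. White participants. Example, men 70-74: 0.9 × (6 + 19.6 + 0.5 × 26.661) = 35.0 per 1000. The corresponding figure for women is 35.9. Averaged over sex at 45% male and 55% female:

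| Age group | Share | Hazard per 1000 |
|---|---|---|
| 70-74 | 50% | 35.5 |
| 75-79 | 30% | 46.8 |
| 80-84 | 15% | 67.2 |
| 85+ | 5% | 117.9 |

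- The overall placebo rate is 47.75. Averaged over both arms it is 47.75 × 0.95 = 45.4, the rate stated in Appendix 2.
- 117.9 / 35.5 = 3.3.
- Under 80: (0.5 × 35.5 + 0.3 × 46.8) / 0.8 = 39.7. At 80 and over: (0.15 × 67.2 + 0.05 × 117.9) / 0.2 = 79.9. The ratio is 2.0.

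**3. Can the rule fire?** 19,000 / 2 = 9,500 per arm.
- Standard error of a standardised mean difference: √(2/9500) = 0.0145. 0.25 / 0.0145 = 17.2 standard errors. For age it is less likely still, because age is stratified.
- Standard error of a log odds ratio: √(2 / (9500 p(1−p))). ln 1.5 divided by this is 14.0 at p = 50%, 8.4 at 10%, 6.1 at 5% and 3.9 at 2%.
- Chance of firing in either direction, by binomial simulation: about 0.01% at 2% prevalence, 0.6% at 1%, 5% at 0.5% and 18% at 0.25%.

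**4. What the threshold would tolerate for age.** With assumed band midpoints of 72.5, 77.5, 82.5 and 88 years, the SD of age is 4.5 years. The rates above imply a log hazard ratio of 0.0692 per year, which is 0.311 per SD (hazard ratio 1.37). An imbalance of 0.25 SD would multiply the unadjusted hazard ratio by exp(0.25 × 0.311) = 1.08, nearly the whole 10% target effect. An imbalance of one standard error gives exp(0.0145 × 0.311) = 1.005.

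**5. What the univariate model costs.** This is a large-sample Cox score calculation with a true hazard ratio of 0.90 within each age and sex group, 5 years of follow-up, an assumed 1% per year censoring, and about 3,705 events. Power = Φ(z − 1.96).

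| Model | Target HR | z | Power |
|---|---|---|---|
| Univariate | 0.9015 | 3.1519 | 88.3% |
| Stratified <80 / ≥80 | 0.9005 | 3.1864 | 89.0% |
| Stratified by four age groups | 0.9000 | 3.2026 | 89.3% |

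- Hand check: z ≈ \|ln HR\| × √(events/4). For the univariate row, 0.1037 × 30.43 = 3.16.
- Equivalent events: (3.1864/3.1519)² = 1.022 and (3.2026/3.1519)² = 1.032. That is 2.2% to 3.2%, or about 82 to 120 events. The drop from 3787 to 3685 events was 102.
- Adding sex to the four age groups leaves power at 89.3%.
- Other follow-up lengths: the gain is 0.7 to 1.0 point at 4.25 years (no censoring) and 0.5 to 0.7 point at 7 years. A separate calculation with 2.25% per year loss, stratified by age group and sex, gives 87.5% rising to 88.5%.
- A 600-replicate simulation with age groups and sex as covariates gave 86.7% unadjusted and 88.0% adjusted, with a Monte Carlo standard error of about 1.4 points.

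**The case against.** The strongest reply is that nothing here is an error. An unadjusted comparison under 1:1 randomisation and intention to treat is valid. The sample size was calculated for exactly this model, and its figures reproduce. The choice between a marginal and an age-conditional hazard ratio is partly a matter of preference, and a shift from 0.900 to 0.9015 is tiny. The rule can also be read as a safeguard against gross imbalance, which the protocol itself does not expect. All of this stands, and it limits the point to efficiency and to a rule that does little.

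A reader might go further and infer any of the following. The document does not support them.
- **That the report would contain no adjusted result.** The dropout sensitivity analysis adjusts for baseline covariates whether or not the rule fires, and the subgroup models in section 7.3.4 contain age. What is missing is a planned, prognostically adjusted estimate of the overall effect.
- **That the rule can never fire.** It can, by chance, for binary factors of about 1% prevalence or less. In that case it would select covariates for their rarity.
- **That the test is invalid or the stated 89% power is wrong.** Ignoring a balanced stratum makes the test slightly conservative and does not inflate type I error. The 89% is correct for a univariate hazard ratio of 0.90, and the protocol does not say whether its 0.90 is marginal or within age groups.
- **That sex or country should also be in the model for precision.** On the Appendix 2 rates the sexes hardly differ within an age group, and no gain from country or region is shown.

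**Conclusion.** The point holds as a modest, free improvement. Section 7.3.2 fixes a treatment-only model although age is a randomisation stratum and, on the protocol's own rates, by far the strongest predictor examined. The imbalance rule cannot realistically bring in age, any quantitative measure, or any binary factor of about 5% prevalence or more.

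The cost is about 0.7 to 1.0 point of power, worth 2% to 3% of events, and a target hazard ratio of about 0.9015 instead of 0.900. It does not threaten the validity of the trial.

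These sizes rest on constant hazards (assumed in Appendix 2), the Australian and U.S. White rates applied to everyone, an assumed 1% per year censoring, and, for the imbalance figures in step 4 only, assumed midpoints of the age bands. A statistical analysis plan that was not available may refine the model, but the protocol text as it stands fixes the univariate one.

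**What to change.** Amend section 7.3.2 before unblinding:
- Stratify the primary Cox model by the randomisation age group (under 80, 80 and over), or adjust it for age. Report the univariate hazard ratio as supportive.
- Replace the 0.25 SD / odds ratio 1.5 rule with a covariate set named in advance and chosen for prognostic value, for the secondary adjusted analyses.
- Country or U.S. region may be added as a stratum for consistency with the randomisation, without expecting a gain. Individual general practices are probably too small to be strata (the protocol gives no practice sizes).

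The cost is a change of wording. Age is already recorded at randomisation (section 7.1.4), no extra participants or data are needed, and the event target can stay. The one downside is that the primary hazard ratio becomes conditional on age. Here that differs from the univariate one by about 0.0015, and reporting both makes the difference visible.
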